**Fig. 1 Fig1:**
[figure not shown]
SPIRIT figure for RELATE trial

#### Intervention

##### Teaching recovery techniques (TRT)

TRT is a 7-session group programme, developed by the Children and War Foundation [34] with five sessions for the young person and two for the caregiver. Carer sessions are timed to coincide with the early young person sessions, so that they can best support their young person through the intervention. The team adapted the TRT manual for use with young people in care (e.g. adapting the case study to be more reflective of the trauma experiences of this population). Due to current UK government restrictions relating to safe working in the context of COVID-19, the intervention will be delivered online. If regulations allow, in-person groups may resume. For virtual groups, a short additional session will be added before the group sessions begin, where each young person can individually meet with the group leaders over video and where important group ‘rules’ can be discussed (e.g. relating to safeguarding processes). All group sessions are 90 min and run weekly (over approximately 5 weeks in total) and will be delivered by two mental health practitioners employed by the specialist CAMHS or social care site and trained in the TRT intervention. The young person sessions will be grouped by age, with a 10–13-year-old group and a 14–17-year-old group, allowing for some clinical and/or social worker judgement (e.g. some 14-year-olds may be better suited to the younger group).

Young person sessions involve understanding intrusive memories (session 1 and the introduction of a case example); intrusive images, worries and dreams (session 2); arousal, emotions and coping (session 3); avoidance, memories and triggers (session 4); and memories and ‘wrapping up’ (session 5). Sessions 1–3 focus on the stabilisation and developing adaptive coping strategies, whilst sessions 4–5 support the young person to develop their maltreatment narrative. The narrative component is an opportunity for young people to order/sequence their memories of their maltreatment, as far as possible, rather than a full narrative exposure, as would be completed over multiple sessions in 1:1 tf-CBT. It can be completed verbally but also through creative mechanisms (e.g. drawing, writing). Embedded in the intervention is a discussion about appropriate verbal disclosures within a group. The same two facilitators conduct each session, so if a young person requires some additional support, or needs to leave the group for a period of time during the session, this can be appropriately supported (e.g. through a facilitator coming away from the computer and calling the young person/their carer). The two caregiver sessions train carers to understand and adaptively support trauma-related distress. The trial aims to include approximately four groups of young people with approximately five to eight young people in each group.

Intervention facilitators will be trained in the intervention by members of the Children and War Foundation training team.

##### Care-as-usual (CAU)

In the CAU condition, social workers will follow their standard care protocol for young people experiencing psychological distress. A typical response may include social workers making a referral to either the specialist local CAMHS or general CAMHS. Referral types and timings, as well as what type of support the young person or carer receives, will be monitored and reported. In any definitive trial, this comparison condition will allow us to explore whether a relatively low-intensity group intervention (TRT) is more effective than the usual support young people in care with elevated PTSD symptoms receive. Young people in this arm can still be referred to the same specialist-CAMHS team as those in the intervention, but over the duration of the trial (until completion of final 3-month follow-ups), they will not be seen by the clinicians that are trained in the TRT programme, to prevent contamination.

#### Treatment fidelity

A key feasibility question for a definitive trial is whether it is feasible to carry out gold-standard fidelity checks (i.e. to explore therapist adherence to the treatment manual). To check fidelity, a randomly selected 30% of TRT sessions will be audio-recorded for fidelity ratings by the research team. Young people and carers will provide informed consent/assent for sections of the study to be audio-recorded. The week prior to an audio-recorded session, young people (and carers) will be informed that the following week’s session will be audio-recorded, unless someone objects to this. The researcher will then call the carers in the days prior to the session and see whether any young person or carer wishes to decline the session being audio-recorded. If one person in the group session declines, the session will not be recorded. Other group members will not be aware who has declined. Whilst it is possible that this will mean that sessions cannot be recorded, and gold-standard fidelity check measures not utilised, this is important information for any future definitive scaled trial. As a second fidelity check, at the completion of a random 30% of the sessions, facilitators will complete a brief checklist highlighting whether they did or did not include key components, and why they did not include key components if this was the case.

#### Measures

##### Eligibility measure

The CRIES-8 [24] is a well-established 8-item screening tool for PTSD. It is validated as a self-report measure for 8 + year-olds, who respond to each item on a 4-point scale: *not at all* (0) *l*, *rarely* (1)*y*, *sometimes* (3), and *often* (5). The measure covers re-experiencing and avoidance symptoms. A score of 17 or above is considered to reflect clinically elevated PTSS [24]. The CRIES-8 has been widely used and validated with multiple groups of trauma-exposed young people (e.g. [28, 31]). In the current study, it will be delivered by the young person’s social worker as part of the site’s routine mental health screening procedures.

##### Descriptive statistics

We will use a CONSORT flow [12] diagram to describe the flow of participants from the initial screening through to follow-up assessments. Basic sample descriptive statistics will be collected via young person report, carer report, and social worker report. Young people and carers will provide basic information on age, sex and year at school. They will also report on whether or not the young person has previously received support for their mental health, and information about the types of support will be captured (e.g. type of service, number of sessions). Social workers will provide information on the age that the young person entered care and the severity of their pre-care maltreatment experiences, using an adapted version of Kaufman’s 5-point Likert scales, covering physical abuse, sexual abuse, emotional abuse, domestic violence and neglect [19].

##### Primary quantitative protocol acceptability outcomes

Descriptive data will be collected on the following:(i)The proportion of potentially eligible children who completed a CRIES-8(ii)Proportion of eligible young people who agree to participate and proportion of caregivers who also agree(iii)Number of participants in each arm who complete each assessment battery (pre-, post-, 3-month follow-up)(iv)The amount of missing data at post-intervention and 3-month follow-up assessments

#### Primary quantitative clinical outcome

##### Child and adolescent trauma screen (CATS [26];)

The primary outcome measure (administered at each assessment point) will be the young person self-report CATS, which has two parts. The first part is a 15-item trauma history checklist, where the young person marks ‘yes’ or ‘no’ to a list of criterion A trauma exposures. The second part is a 20-item DSM-5 PTSD symptom scale, with symptoms rated from 0 (*never*) to 3 (*almost always*)*.* Whilst the primary outcome is symptom change on the self-report CATS, carer report will also be collected as part of the feasibility study and change in symptoms based on carer report, reported as secondary analysis.

##### Secondary clinical outcomes

Secondary clinical outcomes include young person and carer report, unless otherwise specified. All measures will be administered at each assessment point.CRIES-8 (as described previously as the eligibility measure; young person report only).The Child PTSD Symptom Scale – Interview Schedule (CPSS-I [13];). The CPSS-I is a semi-structured diagnostic interview which assesses the history of criterion A traumatic experiences (to identify an index trauma), followed by 20 items assessing DSM-5 PTSD symptoms and 7 items assessing impairment (relating to symptoms). Items are rated, by the interviewer, on a scale from 0 (*not at all*) to 4 (*6 or more times a week/almost always*). This measure will be administered as an interview measure with young people only.Strengths and Difficulties Questionnaire (SDQ [15];). The SDQ is a widely validated 25-item screening questionnaire which measures internalising and externalising difficulties. Here, the measure will be used to index externalising problems. The externalising scale comprises the 5-item conduct problems and 5-item hyperactivity subscales, with each item scored on a 3-point scale from 0 (*not true*) to 2 (*certainly true*), resulting in an overall range of scores from 0 to 10.Short Mood and Feeling Questionnaire (SMFQ [2];). The SMFQ is a 13-item measure of depression symptoms, with each item rated on a 0 (*true*) to 2 (*not true*) scale.

##### Additional secondary clinical outcomes

Questionnaire measures assessing functioning and relationships will also be carried out at each time point, including the following:The Inventory of Parent and Peer Attachment - parent scale (IPPA [3];). The IPPA is a validated young person self-report questionnaire which assesses the quality of relationships between a young person and their friends and caregiver. In the current study, only the scale addressing the young person’s views on the caregiver relationship will be assessed, and the questionnaire has been adapted to use the wording ‘carer’ rather than ‘parent’. The IPPA - parent scale consists of 28 items which measure three subscales: trust, communication and anger and alienation, with items rated on a 1 (*almost never or never*) to 5 (*almost always or always*) scale. This measure will be completed by young people only.The Parent Trauma Response Questionnaire (PTRQ [33];). The PTRQ is a measure of parental appraisals and support style following a child’s experience of trauma. In the current study, we will use the PTRQ support style subscale, with wording amended to reflect carers, rather than parents. The support style subscale consists of 10 items which are rated on a scale from 0 (*not at all*) to 3 (*a lot*) and measures avoidant support style (e.g. *discouraging conversation about potentially traumatic experiences*) and approach support style (e.g. *allowing the young person to talk openly about their experiences*). This measure will be completed by carers only.The Child Health Utility 9D (CHU-9D [29];). The CHU-9D is a self-report measure of health-related quality of life which comprised 9 dimensions (*worried, sad, pain, tired, annoyed, schoolwork, sleep, daily routine* and *ability to join in with activities*). Each dimension is rated on 5 levels indicating increasing levels of severity, e.g. 1 (*I do not feel worried today*) to 5 (*I feel very worried today*). This measure will be completed by young people only.

#### Blinding

Post-intervention assessments will be delivered by a researcher blind to participant allocation and baseline symptom scores.

##### Qualitative measures

Several important feasibility and acceptability questions, for the overall protocol and intervention (see the ‘Aims’ section), will also be assessed via a series of qualitative focus groups and semi-structured 1:1 interviews, completed post-intervention with participants (young people and carers) and service providers (social workers and intervention facilitators).

All young people and carers who were randomised to the intervention arm, including those who withdrew at any point, will be invited to participate in separate 1:1 semi-structured interviews over phone/video. Interviews will focus on how the young person and carer found the intervention (including the online delivery format), whether there were specific components that did or did not work as well, how the carer found supporting the young person over the course of the programme, and general feedback on protocol procedures. To further explore the acceptability of the protocol, at least five participants from the CAU comparison arm will also be invited to participate in short qualitative interviews (over the telephone or by post), to ascertain their views of the recruitment procedures and CAU arm. Reasons for declining to participate will be routinely collected at all stages of the study.

For service -providers, two focus groups will be run, one within social care and one within the specialist CAMHS team. These will focus on experiences of the study protocol (including the online delivery format of the intervention), what did and did not work at different stages, and perceived barriers and how (and/or if) they overcame these.

#### Data analysis plan

##### Quantitative data

Supported by the trial statistician, frequencies and proportions will be used to describe the key feasibility outcomes, such as the number and proportion of young people in care who are screened and then eligible for the study and the number and proportion of young people and carers who consent to randomisation, participate in the different elements of the intervention, and complete outcome measures at baseline and follow-up time points. Descriptive statistics (including means, medians, standard deviations and inter-quartile ranges) will be used to describe numeric outcomes at baseline and follow-up time points by treatment arm. We will also explore the evidence of the promise of the intervention to affect symptoms by presenting post-treatment between-group differences (with confidence intervals). The presence of ceiling/floor effects in the questionnaires will also be explored. Finally, data collected in this feasibility study will also be used to help inform the sample size calculation for a future definitive trial.

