## Methods

### Trial design

This trial will comprise a two-arm feasibility RCT, in which participants will be randomly assigned to either the online TRT intervention or care-as-usual (CAU). Participants will be assessed at three time points during the study: baseline (pre-randomisation), post-intervention (~ 6 weeks from the intervention beginning), and at a 3-month post-intervention follow-up. These methods are based on the RELATE trial protocol (version 4; 3 February 2021).

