Following informed assent or consent, the young person and the carer will complete the baseline assessments (see the ‘Measures’ section). Assessments at each time point can be completed over the phone or video, or in some cases, in person at the young person’s foster or care home, depending on the preference of the young person or carer (and following current Public Health England and University guidance relating to COVID-19). The questionnaires can be completed on paper or online (via a Qualtrics link to the questionnaire pack), whilst the diagnostic interview can be completed virtually, over the phone or in person. Participating young people can complete the self-report questionnaire pack independently or supported by the carer, but if needed (e.g. for younger participants), the researcher can also support the young person to complete the questionnaire pack. This is explored on a case-by-case basis. At the follow-up assessments, if a young person declines the qualitative and diagnostic interview, the questionnaire pack can still be completed online via Qualtrics.

Following the baseline assessment, participants will be randomly allocated to TRT or CAU, in a 1:1 ratio by an independent statistician using a computer-generated allocation sequence. Any young people entering into the trial who live in the same household will be randomised together. Randomisation will be stratified by age group (< 14 years or ≥ 14 years), and if children in the household are in different age groups, the age group of the household will be dictated by the mean age of the children. If randomised to the TRT condition, each child will be offered participation in the next age-appropriate group. The outcome of the randomisation will be shared with participants within 48 h.

For participants in the TRT arm, all baseline assessments will be carried out no more than 1 month prior to the first group session. In circumstances where the first session is more than 1 month after the baseline assessments, the young person and carer will be asked to complete the battery of assessments again before the group commences. See Fig. 1 for SPIRIT figure, which outlines key phases of the trial.

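### The primary clinical outcome is CATS symptom change, but the planned comparison is a post-treatment difference with no baseline adjustment stated

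*Protocol article*

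**What the plan says.** Under Primary quantitative clinical outcome, the protocol article states that "the primary outcome is symptom change on the self-report CATS", and it treats change on the carer report as a secondary analysis.

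The Quantitative data section of the Data analysis plan lists summary statistics by arm at each time point. It then says that the promise of the intervention will be explored by "presenting post-treatment between-group differences (with confidence intervals"). It names no model and no covariates, and uses neither the word raw nor the word adjusted.

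The data needed for adjustment are planned. "The primary outcome measure (administered at each assessment point) will be the young person self-report CATS", and the Trial design section gives the time points as "baseline (pre-randomisation), post-intervention (~ 6 weeks from the intervention beginning), and at a 3-month post-intervention follow-up". Under Recruitment, consent, assessments and randomisation, "participants will be randomly allocated to TRT or CAU, in a 1:1 ratio", and "Randomisation will be stratified by age group (< 14 years or ≥ 14 years").

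**The concern.** The outcome definition points to change from baseline, while the analysis section points to a difference at follow-up. A reader cannot tell which number will be reported as the main clinical result, and the two can differ noticeably in a trial of 50. If the choice stays open until the data are in, it can be made with the results in view.

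Precision is also at stake. Baseline CATS is usually informative about later CATS, and with about 25 per arm some chance imbalance at baseline is likely. An analysis that makes no use of baseline gives up precision and carries part of that imbalance into the estimate. The Aims section also wants variances for sizing the full trial. If that trial is to be baseline-adjusted, the relevant quantities are the residual SD and the baseline-to-follow-up correlation, and the article lists neither as an output.

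**Working it through.** **Figure to reproduce.** The article gives no power, SD, effect size or interval width for CATS; the Sample size section says that a power calculation is not appropriate. The only figure is 50 in total, and 50 / 2 = 25 per arm agrees with the text.

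**Inputs from the article.** n = 25 v 25. For a low-retention case, the Key feasibility outcomes thresholds of 60% (TRT) and 50% (CAU) give 0.60 × 25 = 15 and 0.50 × 25 = 12.5, taken as 13.

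**Assumptions.** Two-sided 95% level; equal SD at baseline and follow-up; r from 0 to 0.7; no prognostic value credited to age stratum; independent participants. Siblings allocated together and group delivery are ignored; allowing for them would widen the intervals with or without adjustment.

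**Formulas, in SD units.**
- SE factor: s = sqrt(1/n1 + 1/n2), which is 0.283 at 25 v 25 and 0.379 at 15 v 13.
- Unadjusted post-treatment difference: t(n1+n2−2) × s. At 25 v 25: 2.011 × 0.283 = 0.569.
- Change score: the unadjusted half-width × sqrt(2(1−r)). At r = 0.3: 0.569 × sqrt(1.4) = 0.673.
- Adjusted for baseline and age stratum: t(n1+n2−4) × s × sqrt(1−r²) × sqrt(1 + 2/(n1+n2−5)). The last factor is the expected cost of estimating two covariate effects. At 25 v 25 and r = 0.5: 2.013 × 0.283 × 0.866 × 1.022 = 0.504.

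**95% half-widths (SD units).**

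| r | 25 v 25: unadjusted | change score | adjusted | 15 v 13: unadjusted | change score | adjusted |
|---|---|---|---|---|---|---|
| 0 | 0.569 | 0.804 | 0.582 | 0.779 | 1.102 | 0.815 |
| 0.3 | 0.569 | 0.673 | 0.555 | 0.779 | 0.922 | 0.778 |
| 0.5 | 0.569 | 0.569 | 0.504 | 0.779 | 0.779 | 0.706 |
| 0.7 | 0.569 | 0.441 | 0.416 | 0.779 | 0.603 | 0.582 |

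At 25 v 25, adjustment narrows the interval by 2%, 11% and 27% at r = 0.3, 0.5 and 0.7. At 15 v 13 the gains are 0%, 9% and 25%. At r = 0 adjustment costs 2% and 5% respectively. The change score is wider than the unadjusted difference whenever r < 0.5.

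**Chance imbalance.** The baseline mean difference has SE 0.283 SD at 25 v 25, so P(|difference| > 0.3 SD) = 2(1 − Φ(0.3/0.283)) = 0.29. At 15 v 13 it is 2(1 − Φ(0.3/0.379)) = 0.43. Given an imbalance d, the unadjusted difference shifts by r × d: for d = 0.3 SD, 0.5 × 0.3 = 0.15 SD, or 0.7 × 0.3 = 0.21 SD. A change score shifts the other way, by (1−r) × d, which is also 0.15 SD at r = 0.5.

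**Sizing the full trial.** The variance of an adjusted comparison scales by about 1 − r². That is 1 − 0.25 = 0.75 at r = 0.5 (about 25% fewer participants) and 1 − 0.49 = 0.51 at r = 0.7 (about 49% fewer).

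**The case against.** The strongest reply is that the article never says the difference is unadjusted. A reader might infer a firm commitment to a raw comparison that discards baseline, since the sentence follows directly on means and SDs by arm. The documents do not support that: an adjusted post-treatment difference fits the same words, and covariates are commonly left to an analysis plan, which is not shown here. Silence on the model is therefore not an error in itself.

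It can also be said that the two sections do not target different effects. With a baseline taken before randomisation, the expected between-arm difference in change equals the expected difference at follow-up. That is correct. The mismatch lies in the estimator, not in the underlying effect, and it bears on precision and on the number that is reported.

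Three further limits stand:
- Imbalance does not pass into the estimate in full, only r times its size, and on average over randomisations the unadjusted interval already allows for it.
- The correlation could still be computed, because the article says that the collected data will inform the later sample size and CATS is given at every assessment.
- The gain depends on r, which the article does not give.

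What these replies leave untouched is that the article names change as the outcome and a post-treatment difference as the analysis, without saying how the two connect.

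**Conclusion.** The point holds as a mismatch that should be reconciled, with a clear gain in precision available. The outcome definition and the analysis section leave two estimators open for the primary clinical outcome, and these perform differently: at r = 0.3 and 25 per arm, the half-width is 0.67 SD for a change score and 0.57 SD for an unadjusted difference. Baseline adjustment is better than both at moderate or high r (0.50 at r = 0.5, 0.42 at r = 0.7) and costs at most 2% to 5% if baseline carries no information. It would be too strong to call the planned interval needlessly wide, since that depends on an assumed correlation and on adjustment not being intended.

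The consequence is modest. The comparison is exploratory, and none of the three questions under Key feasibility outcomes (screening, group size, retention) uses a symptom difference. What is affected is the clarity and precision of the evidence-of-promise estimate and the inputs for the full trial.

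**What to change.** In the Quantitative data section, state that the TRT minus CAU difference in self-report CATS at post-intervention and at 3 months, with 95% confidence interval, comes from a linear model adjusted for pre-randomisation CATS and the age stratum used at randomisation. If this is already intended, saying so is enough.

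Align the sentence under Primary quantitative clinical outcome with that definition. Switching to unadjusted change scores is not the way to reconcile the two, since it would widen the interval if r is below 0.5.

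Specify that the baseline is the pre-randomisation one. The recruitment section describes a repeat battery for the TRT arm only, when the first session falls more than a month after baseline, and that repeat may come after randomisation.

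Report the residual SD and the baseline-to-follow-up correlation for the definitive sample size.

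The cost is wording only; all the data are already planned.
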